### Attendance, fidelity and adherence

Psychologists completed a post-session online log for every attended session, where they recorded whether the client attended (attendance – yes/no) and whether they were able to conduct the session in the intended setting (fidelity – yes/no). In addition, using a scale created for the purpose of this study, psychologists reported how well they aligned with a non-directive supportive therapy approach during the session (adherence – scale where 0=no adherence to 10=complete adherence).

### Costs

The costs of delivering walk-and-talk (outdoor group) and usual care (indoor group), including psychologist, other staff time and space requirements, were recorded. Health service use data (eg, GP visits, emergency presentations, hospital admission, etc, during the last 5 months) were collected using client self-report. Costs related to service use were derived from publicly available sources including Medicare Benefits Schedule, and Pharmaceutical Benefits Scheme item codes and Diagnosis-Related Groups (for hospitalisation data).

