#### Interventions

In both conditions, participants were invited to attend 10 fortnightly 60-minute individual psychotherapy sessions over 20 weeks. Participants were scheduled to attend one session per fortnight on the same day and time, with the same psychologist and within their allocated condition. If a participant missed a session, they were offered the opportunity to reschedule with the same psychologist within a time slot allocated to their assigned treatment condition, pending psychologist availability. There was no cost to participants for the sessions.

The sessions were delivered by provisionally registered (n=1) or registered (n=12) psychologists. The provisional psychologist received weekly supervision from a senior registered clinical psychologist during the trial. To prevent confounding, all psychologists delivered therapy in both study arms. Members of the research team delivered a half-day training session for the psychologists prior to working with participants, which involved walking the therapy route, contingency planning, strategies for maintaining safety and confidentiality and details on the proposed therapy style.

The sessions involved a non‐directive supportive therapy style using counselling micro‐skills to address important issues identified by the participant.^39^ This approach remained consistent in each study arm and was selected for the current study for several reasons: (1) it could be feasibly delivered in both indoor and outdoor environments (compared with other approaches which require access to worksheets, manuals or other resources), (2) it maintained the focus of the trial on the experimental manipulation (ie, the conventional indoor vs walk-and-talk context), (3) all psychologists in Australia are required to demonstrate competency with this approach during their training and (4) it is effective for treating depression.^39
40^

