### Measures

Participants completed three online surveys (baseline, post-intervention at 5 months and 12-month follow-up) via QuestionPro, a secure online survey platform licensed by the University of Newcastle. The baseline survey was completed after all participants were enrolled and prior to their first therapy session. The post-intervention survey was completed approximately 1 week after their last therapy session (which was at 5 months post baseline), and the follow-up survey will be completed at 12 months post baseline. Participants will receive an email containing a personalised survey link at each time point. To promote retention and maximise completions at post-study and follow-up, participants who have not responded within 1 week will receive a reminder email, followed by a reminder telephone call and text message if needed. Participants who remain unresponsive will be sent an abbreviated survey containing the primary outcome measure only (DASS-21), consistent with an intention-to-treat approach. At the end of each week, survey data will be exported from QuestionPro and imported into a password-protected database stored on a secure University of Newcastle OneDrive server. All identifying information will be replaced with a unique numerical participant code prior to analysis; however, a separate password-protected linkage file will be retained by the research team to enable longitudinal data linkage across time points. Only members of the research team will have access to identifiable data.

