### Sample size

A sample size of 56 per group at 5 months would provide 80% power to detect a between group difference (in change score) of 8 units in overall psychological distress (DASS-21, α=0.05, SD change=15 units). This aligns with our pilot effect, which also represented an 18% reduction in baseline symptoms.^33^ While this is at the lower threshold of clinical significance, we expect this difference will be evident above any improvements reported by the conventional indoor therapy condition. In another trial targeting men with low mood, a 21% attrition was experienced over 6 months.^47^ Based on this, we conservatively estimated a 25% attrition rate at 5 months (the primary endpoint). To ensure complete data from 56 men per group at 5 months, we aimed to randomise at least 150 men into the trial (ie, 75 per group).

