#### Cost-effectiveness analysis plan

A trial-based cost-utility analysis will be undertaken from the perspective of the health service over a 12-month period. Health utility of patients over the duration of the study will be derived from their SF-12 scores, and quality-adjusted life-years gained will be calculated. Costs of the intervention and health service use will be compared across the two groups and an incremental cost-effectiveness ratio (showing differences in costs and quality-adjusted life years gained) will be calculated. Sensitivity analyses, including probabilistic analyses will be used to assess the robustness of results to uncertainty in estimates of costs and health outcomes.

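### As written, the 5-month recall window for self-reported service use cannot cover the 12-month cost-utility horizon with surveys at 0, 5 and 12 months

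*Protocol article*

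**What the plan says.** The Costs section of the protocol article describes two cost sources. Delivery costs in both arms, "including psychologist, other staff time and space requirements, were recorded", come from the study itself. Other service use comes from participants: "Health service use data (eg, GP visits, emergency presentations, hospital admission, etc, during the last 5 months) were collected using client self-report". That is the only recall window given. The section does not say at which surveys the question is put, and Table 1 does not list service use.

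The Measures section sets the possible collection points: "Participants completed three online surveys (baseline, post-intervention at 5 months and 12-month follow-up) via QuestionPro". It adds that "the follow-up survey will be completed at 12 months post baseline".

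The Cost-effectiveness analysis plan sets the horizon: "A trial-based cost-utility analysis will be undertaken from the perspective of the health service over a 12-month period". It then says that "Costs of the intervention and health service use will be compared across the two groups", and that the difference in cost enters the incremental cost-effectiveness ratio together with QALYs derived from the SF-12. Table 1 has the SF-12 at all three surveys.

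**The concern.** The two follow-up surveys are 7 months apart at the end of the year, but the stated recall reaches back only 5 months. A fixed 5-month question therefore cannot account for a full year of service use, whichever of the stated surveys carry it. The SF-12 utilities do span the year. The cost and QALY parts of the ratio would then refer to different lengths of time, although the result would be presented as a 12-month cost-utility estimate. The Discussion names cost-utility among the evidence that is to inform whether walk-and-talk therapy enters routine practice, so readers will use that estimate.

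Timing matters too. An analysis plan can extrapolate over months that nobody was asked about, but it cannot recover them. According to the Study design section, 12-month assessments are still in progress.

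**Working it through.** **Inputs**
- Recall window: 5 months (Costs).
- Survey times: 0, 5 and 12 months (Measures).
- Horizon: 12 months (Cost-effectiveness analysis plan).
- Treatment period: "10 fortnightly 60-minute individual psychotherapy sessions over 20 weeks" (Interventions).

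**Coverage.** A survey at month t with recall r covers the interval from t − r to t, cut at month 0. Total coverage is the union of these intervals within months 0 to 12.

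| Survey(s) carrying the item | Months covered | Total | Missing | Share of horizon |
|---|---|---|---|---|
| 5 and 12 months | 0-5 and 7-12 | 10 | 2 (months 5-7) | 2/12 = 16.7% |
| 5 months only | 0-5 | 5 | 7 (months 5-12) | 7/12 = 58.3% |
| 12 months only | 7-12 | 5 | 7 (months 0-7) | 7/12 = 58.3% |

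Asking at baseline as well adds nothing, because that answer describes time before the trial. The stated 12 months is not reproduced under any schedule. The smallest gap is 2 months, and months 5-7 are uncovered in every row. Within the 7 months between the follow-up surveys, the smallest gap is 2/7 = 28.6%.

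**Can another stated source fill the gap?**
- Delivery costs cannot. Treatment lasts 20 weeks, that is 20 × 7 = 140 days, or 140/30.4 = 4.6 months, all within months 0-5.
- The public schedules and diagnosis-related groups named under Costs supply prices. The quantity of use is self-reported.
- No linkage to claims or hospital records is described, and no extrapolation rule is stated.

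**What closes it.** With 5 months of recall at the 5-month survey and 7 months at the 12-month survey, coverage is 5 + 7 = 12 months and the gap is 0.

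**Effect on the cost figures.** If use accrued evenly over the year, each arm's self-reported service cost, and the between-arm difference in it, would be understated by the shares in the table. Even accrual is an assumption, and the documents give no data on it.

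**The case against.** The strongest reply is that the 12-month questionnaire is not shown. The Study design section says that the 5-month assessments are complete and the 12-month ones are not. A past-tense sentence about the last 5 months fits the completed 5-month survey, for which 5 months is exactly the right window. The later form may well ask about 7 months. This stands in part. A reader might infer that use in months 5-7 was never collected, and the article does not establish that. Tense does not settle it either, since the Measures section also uses the past tense for all three surveys.

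A second reply is that item wording by time point, and the handling of uncovered months, are usually left to a full protocol or health-economic plan. That is fair for what is merely absent. Here, however, the article states a window and a horizon that do not match.

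A third reply concerns bias. It is tempting to argue that the gap opens just as the free sessions stop, so that men then seek other care and the omission cannot be neutral. The documents do not support this. Both arms are offered the same 10 free sessions over the same 20 weeks, so any later rise in use could be similar in both arms and largely cancel in the incremental cost. The argument also conflicts with the even-accrual assumption behind the percentage shares.

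Finally, the cost-utility analysis is not the primary analysis. That is correct and limits the severity.

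**Conclusion.** The mismatch is real as the article is written. At best 10 of 12 months of self-reported service use are covered, with months 5-7 missing (17%). If the item is asked at only one follow-up survey, 7 of 12 months are missing (58%). These figures rest on the 5-month window applying wherever the question is asked, and on there being no source of use data beyond those described.

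The finding does not show that data have been lost, and it does not show a bias for or against either arm. The direction and size of any effect on the between-arm cost difference are unknown. It concerns only the self-reported service-use component of a secondary analysis. Intervention delivery costs, the DASS-21 primary outcome and its sample size are untouched. It should be fixed, with some urgency because part of the remedy lapses as 12-month surveys are returned, but it does not threaten the trial's main result.

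**What to change.** 1. **Check first.** Read the 12-month questionnaire, then state in the Costs section which surveys ask about service use and over what period. If the 12-month form already covers 7 months, this correction of the text is all that is needed.

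2. **If it asks about 5 months.** Change forms not yet sent so that they ask about use since the 5-month survey (7 months). For forms already returned, pre-specify a base case of C(0-5) + C(7-12) × 7/5, where C is the service cost in the months shown. This assumes that the monthly rate in months 5-7 equals that in months 7-12. Because that is untested, add a sensitivity analysis with C(0-5) + C(7-12) × (1 + 2k/5), varying k, the ratio of the two monthly rates. Setting k = 1 returns 7/5, and k = 0 gives the unscaled sum.

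3. **If it does not ask at all.** Add the item, with 7-month recall, to unsent forms. For participants without it, limit the service-cost comparison to 5 months or label the later months as extrapolated.

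4. **Report the coverage** of the 12-month horizon achieved in each arm.

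The cost is one change of survey wording, submitted to the ethics committee and entered in the registry as the Study design section requires, plus a short analysis step. The downside is that longer recall is less accurate and that recall length may differ by cohort. Randomisation was within cohort, so the arms stay comparable if the new wording is introduced in both arms at the same time.

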### Demographics

To examine the representativeness of the sample, participants provided demographic information including age, self-reported employment status, education level, country of birth, ethnicity, primary language, marital status and whether they were Aboriginal and/or Torres Strait Islander. Participants also reported how they heard about the study (eg, social media ad, radio interview, flyer).

### Sample size

A sample size of 56 per group at 5 months would provide 80% power to detect a between group difference (in change score) of 8 units in overall psychological distress (DASS-21, α=0.05, SD change=15 units). This aligns with our pilot effect, which also represented an 18% reduction in baseline symptoms.^33^ While this is at the lower threshold of clinical significance, we expect this difference will be evident above any improvements reported by the conventional indoor therapy condition. In another trial targeting men with low mood, a 21% attrition was experienced over 6 months.^47^ Based on this, we conservatively estimated a 25% attrition rate at 5 months (the primary endpoint). To ensure complete data from 56 men per group at 5 months, we aimed to randomise at least 150 men into the trial (ie, 75 per group).

### Patient and public involvement

A lived experience representative and end-user (EW) was involved in this study as an associate investigator from the grant application stage and is a coauthor on this protocol. His involvement included input into study design, including selection of outcome measures based on lived experience and relevance to participants. EW also reviewed and provided feedback on participant-facing materials, including recruitment materials, participant information statements and written communication templates. EW will continue to be involved throughout the trial, including interpretation of findings and contribution to dissemination outputs, and will be included as a coauthor on resulting trial publications. In addition, the study design was informed by feedback from men with lived experience who participated in a preregistered pilot study.^33^ Based on feedback regarding burden and engagement, the intervention was refined from weekly to fortnightly sessions and extended in duration to better align with participant preferences.

The trial was co-designed with health service stakeholders, including a clinical psychologist representing Hunter New England Mental Health, who contributed to the intervention schedule, psychologist recruitment and harm monitoring procedures. Trial governance is provided by an Executive Committee comprising all investigators and the postdoctoral researcher, who met regularly to monitor progress. An End-User Committee (chief investigator, postdoctoral researcher, lived experience representative, external clinical psychologist) will meet biannually to provide independent oversight, review progress against milestones and contribute to interpretation of findings and coauthorship of trial publications. A formal Data Monitoring Committee was not established due to the low-risk nature of both interventions (standard individual psychological counselling differing only in setting), the absence of pharmacological risk and the short duration of each phase. Interim data were not made available to investigators or external parties during the trial period to preserve outcome assessment integrity.

### Statistical methods

#### Primary analysis plan

Linear mixed models will examine the primary and secondary outcomes for the impact of group, time (categorical) and the group-by-time interaction. This approach ensures outcomes for participants lost to follow-up are modelled in the analyses, consistent with an intention-to-treat approach. To adjust for potential baseline differences, age, socio-economic status, baseline physical health (Short Form-12 survey (SF-12) physical subscale) and baseline depression treatment (ie, concurrent use of antidepressant medication and/or external psychotherapy) will be examined to determine whether they contribute significantly to the models. If a covariate is significant, a term will be added to the model to adjust for the effects and two-way interactions with time and treatment will also be examined. If these interactions are significant, they will also be adjusted for. For the primary outcome, we will conduct a sensitivity analysis to explore the impact of adjusting for participants’ prerandomisation treatment expectancies (for the arm they were subsequently randomised to) on the group-by-time intervention effect. A post-hoc sensitivity analysis will also be conducted to account for therapist-level clustering by modelling therapist as a random intercept term, enabling direct comparison of results with and without this effect.

As the analyses of secondary outcomes are intended to complement the primary outcome data and provide preliminary insights for future hypothesis testing, no multiplicity adjustments will be conducted. Given the exploratory nature of these secondary analyses, p values <0.05 will be interpreted as suggestive, rather than significant effects for these outcomes. Effect sizes will be calculated using Cohen’s *d* and interpreted as small (*d*=0.2), medium (*d*=0.5) or large (*d*=0.8).^48^

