**Methods and analysis:**

This assessor-blinded, parallel group randomised controlled trial is comparing the efficacy of walk-and-talk therapy to conventional indoor therapy for men with depressive symptoms. After randomisation, all participants receive 10 fortnightly 1-hour individual psychotherapy sessions over 20 weeks as either: (1) conventional indoor therapy (sitting down indoors) or (2) walk-and-talk therapy (walking outdoors). Participants are assessed at ‘pre-intervention’ (baseline), ‘post-intervention’ (5 months post baseline) and ‘follow-up’ (12 months post baseline) time points. The primary outcome is change in overall psychological distress (21-item version of the Depression, Anxiety and Stress Scale (DASS-21)) at post-intervention. Secondary outcomes include male-type depression symptoms, mental well-being, suicidal ideation and quality of life. Costing data is being collected for cost-effectiveness analysis. Linear mixed models will be used to examine the impact of group (conventional indoor vs walk-and-talk), time (baseline, 5-month and 12-month) and the group-by-time interaction for primary and secondary outcomes.

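### The primary mixed model lets baseline DASS-21 means differ by arm, giving up precision that randomisation provides free; a common baseline mean would recover it

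*Protocol article*

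**What the plan says.** The Primary analysis plan section specifies the model: "Linear mixed models will examine the primary and secondary outcomes for the impact of group, time (categorical) and the group-by-time interaction". The abstract gives the time levels: "time (baseline, 5-month and 12-month) and the group-by-time interaction for primary and secondary outcomes". Baseline is therefore a response level, and the group main effect allows the arms different baseline means. The candidate covariates are age, socio-economic status, SF-12 physical health and baseline depression treatment. Baseline DASS-21 is not listed.

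The endpoint is clear elsewhere. The abstract says: "The primary outcome is change in overall psychological distress (21-item version of the Depression, Anxiety and Stress Scale (DASS-21)) at post-intervention". The Sample size section calls 5 months the primary endpoint and states: "A sample size of 56 per group at 5 months would provide 80% power to detect a between group difference (in change score) of 8". The assumptions it gives for this are "DASS-21, α=0.05, SD change=15 units". It adds 25% attrition, giving 75 men randomised per group. The Randomisation and allocation section says that allocation followed completion of baseline assessment by all participants in a cohort.

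**The concern.** Allocation came after baseline measurement, so any baseline DASS-21 difference between arms is due to chance. A model with a free baseline mean in each arm ignores this. With complete data, its 5-month group-by-time coefficient is the plain difference in mean change. That contrast subtracts the whole chance imbalance, when only a fraction rho (the baseline-to-5-month correlation, with equal variances) is expected to persist. Each unit of imbalance thus shifts the estimate by 1 - rho units, which is 0.5 to 0.2 for rho of 0.5 to 0.8. The estimator remains unbiased over repeated randomisations but is noisier than it needs to be.

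The analysis text also speaks only of the group-by-time interaction. With three categorical visits that term has two degrees of freedom, whereas the endpoint and sample size concern 5 months alone. What is at stake is power on the primary question and a clear link between the model and the powered comparison.

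**Working it through.** **Inputs.** From the Sample size section: difference 8, SD of change 15, alpha 0.05, 56 per group analysed, 75 per group randomised. The document does not give rho; 0.5 to 0.8 is assumed, with equal variances at baseline and 5 months. The implied DASS-21 SD is 15/sqrt(2(1 - rho)), which is 15.0, 19.4 and 23.7 for rho 0.5, 0.7 and 0.8. Power uses the two-sided normal approximation unless stated.

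**1. The plan's own figure.** n = 2 × 15² × (1.960 + 0.842)² / 8² = 55.2, so 56 per group. 56/0.75 = 74.7, so 75. Both figures reproduce. A one-sided test would need only 44, so the calculation is two-sided. Power at 56 is 80.6% (79.9% by noncentral t).

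**2. The planned model, complete data.** SE of the 5-month interaction coefficient = 15 × sqrt(2/56) = 2.835. This is the change-score SE used in step 1, so power is again 80.6%.

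**3. The planned model with the planned attrition.** Men with baseline only still contribute. With 75 per arm at baseline and 56 at 5 months, the variance is 225 × [(1 + rho)/56 + (1 - rho)/75].

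**4. Common baseline mean.** The variance is 225 × (1 + rho)/56. Relative to the complete-data change score, 225 × 2/56, the ratio is (1 + rho)/2.

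| rho (assumed) | SE, free baseline | Power | SE, common baseline | Power |
|---|---|---|---|---|
| 0.5 | 2.743 | 83.0% | 2.455 | 90.3% |
| 0.7 | 2.780 | 82.1% | 2.613 | 86.5% |
| 0.8 | 2.799 | 81.6% | 2.689 | 84.5% |

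The gain is about 7, 4 and 3 percentage points.

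**5. If the interaction were read as a joint test.** Assume 56 per arm at both visits, SD of change 15 at each, a 5-month difference of 8, and a correlation of 0.4 to 0.7 between the two changes. The noncentrality is 28 × d'V⁻¹d, where d holds the 5- and 12-month differences and V is the covariance matrix of the two changes. The test is F(2,110).

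| 12-month difference (assumed) | Power of joint test |
|---|---|
| 8 | 78-86% |
| 6 | 71-77% |
| 4 | 70-74% |
| 0 | 78-95% |

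With no 5-month difference and 8 units at 12 months, the joint test still rejects with probability 78-95%. It would not isolate the primary endpoint.

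**The case against.** The strongest reply is that nothing is broken. The endpoint, the sample size and the 5-month coefficient of the planned model all describe the same quantity, a difference in change at 5 months. The planned power is met as written, and slightly exceeded once baseline-only men are counted. This stands in full.

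A reader might infer that the joint two-degree-of-freedom test decides the trial and that it is underpowered. The document does not support this. The analysis section lists model terms and never says that a joint test decides, while the abstract and the Sample size section point to 5 months. An article may also leave the exact contrast to the full plan, so the unnamed contrast would not be a finding by itself. Nor can it be said that a joint test would miss an effect that has gone by 12 months: its power is then 78-95%. The dip is confined to partial fading.

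A reader might also infer that the baseline measurement is wasted. It is not: it enters as the first repeated measure, and the effect is change from it. Because it is already a response level, its absence from the covariate list is not a separate fault.

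It is also fair to say that rho is assumed, that the gain over the mixed model as planned is only about 3 to 7 points, and that changing a preregistered model after post-intervention assessments are complete has a credibility cost. These limit the size of the point. They do not remove it, because the free baseline means are a stated feature of the model and randomisation gives no reason to keep them.

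**Conclusion.** The concern holds as a matter of efficiency. The planned analysis is valid and the sample size is correct for it, but free baseline means cost precision that a common mean would recover. Power at 5 months would rise from about 82-83% to 84-90% with the same men. This rests on assumed correlations of 0.5 to 0.8, equal variances, and the planned 75 and 56 per arm. The Discussion concedes that the power calculation left out therapist clustering, so the extra precision has a use.

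Naming the 5-month contrast is a clarification to make in the same edit. It would rule out a reading under which power could be about 70-77%, if the 12-month difference were 4 to 6 units and the two changes correlated at 0.4 to 0.7. It does not correct a stated joint test.

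**What to change.** Before any allocation-linked outcome data are analysed, respecify the primary model with one baseline mean common to both arms: time, plus group-by-time terms at 5 and 12 months, no group main effect, and unstructured covariance. Baseline-only men still contribute.

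Alternatively, take baseline DASS-21 out of the response and adjust for it as a covariate. The two forms match only if baseline leaves the response, and men with baseline only then no longer contribute. Use the same form for secondary outcomes that have a baseline measurement.

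In the same text, name the 5-month between-group contrast (one degree of freedom, two-sided 0.05) as the primary test and the 12-month contrast as secondary.

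No new data or participants are needed. The cost is a dated, documented change to a preregistered model. Reporting the preregistered model as a sensitivity analysis would meet it. The Patient and public involvement section says that interim data were not made available to investigators, which helps the change to be made credibly now.

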## Methods

### Study design

The study design is a parallel-group superiority randomised trial repeated across three cohorts. In each cohort, participants are assessed at baseline, 5 months (post-intervention) and 12 months (follow-up). After completing baseline measures, participants were randomly allocated to either conventional indoor therapy (sitting down indoors) or walk-and-talk therapy (walking outdoors). At the time of writing, recruitment, intervention delivery and post-intervention assessments have been completed across all three cohorts, with 12-month follow-up assessments currently underway. The study was approved by the University of Newcastle Human Research Ethics Committee (HREC) (H-2024-0090) and was prospectively registered with the Australian New Zealand Clinical Trials Registry (ACTRN12624000794505, ANZCTR - Registration, 27 June 2024). Any modifications to the study protocol would be submitted to HREC for approval prior to implementation and updated in the publicly available trial registry. No substantial protocol amendments have been made up to this point. All participants receive $A10 vouchers for completing the post-intervention survey at 5 months and follow-up survey at 12 months ($A20 in total). The reporting of this study will adhere to the Consolidated Standards of Reporting Trials (CONSORT) guidelines.^34^

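### The primary mixed model admits covariates and their interactions only if significant, so it is not fixed before analysis and its adjustment of the group-by-time contrast depends on the wrong test

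*Protocol article*

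**What the plan says.** The Primary analysis plan section of the protocol article sets the model: "Linear mixed models will examine the primary and secondary outcomes for the impact of group, time (categorical) and the group-by-time interaction". Time has three levels: baseline, 5 months and 12 months. The section then turns to adjustment: "To adjust for potential baseline differences, age, socio-economic status, baseline physical health", followed by concurrent depression treatment at baseline. These four "will be examined to determine whether they contribute significantly to the models".

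The rule runs in two steps. First, "If a covariate is significant, a term will be added to the model to adjust for the effects". For a covariate that passes, "two-way interactions with time and treatment will also be examined", and "If these interactions are significant, they will also be adjusted for".

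Two sensitivity analyses are named in that section, one for treatment expectancies and one for therapist clustering. Neither compares the primary result with and without the selected covariates.

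On timing, the Study design section reports that "recruitment, intervention delivery and post-intervention assessments have been completed across all three cohorts". The Patient and public involvement section adds: "Interim data were not made available to investigators or external parties during the trial period".

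**The concern.** There are two separate problems.

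1. **The model is open.** Whether a covariate contributes significantly can be judged only from outcome data. The candidates and the rule are stated in advance, but the model that will deliver the primary p-value is not. A reader of the results could not tell what the selection did.

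2. **The gate tests the wrong thing.** The intervention effect is the group-by-time contrast. A covariate improves that contrast when it predicts change, but the first test asks about its main effect, which is its association with the average level across visits. A covariate can predict who improves without predicting who scores high overall. Such a covariate is stopped at the first step, and its time interaction is never examined.

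What is at stake is a clear confirmatory model, plus precision that the trial could have at no extra recruitment. The sample size was set at 80% power with no allowance for covariates.

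**Working it through.** **Step 1. Reproduce the plan's sample size.** Inputs from the Sample size section: difference in change 8, SD of change 15, alpha 0.05 (taken as two-sided), power 80%, attrition 25%.

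- n per group = 2 × (1.960 + 0.842)² × 15² / 8² = 55.2, rounded up to 56.
- 56 / 0.75 = 74.7, rounded up to 75 per group, or 150 in all.
- Power at 56 per group is 80.6% by the normal formula and 79.9% by the t distribution.

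The plan's figures reproduce. They describe an unadjusted comparison of change scores.

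**Step 2. How open is the model?** Each of four covariates can end in one of five states: out, main effect only, plus time, plus treatment, or plus both. That allows 5⁴ = 625 models. With complete data only the presence or absence of each time term matters for the contrast (step 3), so at most 2⁴ = 16 of them give different answers. If no covariate is related to outcome and each is tested at an assumed 0.05, the chance that at least one enters is 1 − 0.95⁴ = 18.5%.

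**Step 3. Which terms can move the group-by-5-month contrast?** Let x be a baseline covariate and g the group.

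- A term βx is the same at every visit, so it cancels from the 5-month-minus-baseline difference.
- A two-way term γxg is also constant over visits and cancels too.
- A term δx at the 5-month visit does not cancel. It is the only kind that adjusts the contrast.

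A generalised least squares check on one simulated data set (three visits, complete data) gave a contrast of 2.3113 with no covariate, with x, and with x plus x-by-group. Adding x-by-time moved it to 2.1050, and adding x-by-group to that model left it at 2.1050.

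**Step 4. What could fixed adjustment gain?** Assume four mutually independent covariates, each with correlation r with change. The residual SD is 15 × √(1 − 4r²), and the SE is that SD × √(2/56).

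| r with change | Residual SD | SE | 8 / SE | Approximate power |
|---|---|---|---|---|
| 0 | 15.0 | 2.83 | 2.82 | 80% |
| 0.2 | 13.7 | 2.60 | 3.08 | 86% |
| 0.3 | 12.0 | 2.27 | 3.53 | 94% |

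These are ceilings. Chance imbalance in the covariates takes about one point off each adjusted row.

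**Step 5. What does the rule deliver?** Simulation with 56 per group, SD of change 15, difference 8, complete data, one-at-a-time testing at 0.05, main effect first and time interaction second:

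| Assumed correlations | Power, rule as stated | Power, all four fixed with time terms |
|---|---|---|
| 0.2 with level and with change | 81–82% | 84–85% |
| 0.3 with change, none with level | 81% | 93% |
| Unrelated to outcome | 80% | 78–79% |

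Ranges are across separate simulation runs. In the second row each covariate's time term entered in only about 5% of trials, because the main-effect test stopped it.

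**Step 6. Type I error of the group-by-time contrast.** Across the assumed scenarios it was 4.6–5.8% under the rule and 4.4–5.7% with all four fixed, with Monte Carlo error of about 0.3 points. In the run that gave 5.8% under the rule, the unadjusted model also gave 5.8%.

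**The case against.** The strongest reply is that the harm is small and the rule is prespecified. The candidates and the procedure are both written down, the plan is described as preregistered, and the group-by-time contrast already removes baseline differences in outcome level. Covariate-by-time terms are examined, so the plan does not ignore the route that matters. All of this stands, and it limits the point to an open model and a badly placed gate. The 81% against 93% comparison also needs covariates strongly related to change and unrelated to level. No figure in the article supports or excludes that.

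A second reply is that changing the primary model after the 5-month data were collected is itself a risk to credibility. That is fair, and it governs how the fix must be made.

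Three stronger readings are tempting, and the document supports none of them:

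- A reader might infer that the primary test is seriously anti-conservative. Step 6 shows otherwise for the plan's contrast. Simulated error rates of 6.2–10.5% arise in a different analysis, the 5-month score adjusted for baseline with uncentred covariates and a selected treatment interaction. The article does not describe that model.
- A reader might infer that a selected covariate-by-treatment term makes the reported effect conditional on a covariate value. The rule admits only two-way terms, and step 3 shows that such a term leaves the contrast unchanged with complete data.
- A reader might infer that the investigators chose the rule knowing the results. The article says that data collection at 5 months was complete and that interim data were withheld. It does not show that anyone had seen outcomes by arm.

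**Conclusion.** The point holds in limited form. The article states a significance-based rule for the primary outcome, so this is a stated method and not a detail left to an unseen analysis plan. The confirmatory model is not fixed, and the only terms able to adjust the contrast are reached through a test of something else.

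The cost is mainly precision: about 3 points of power at an assumed correlation of 0.2 with level and change, and about 12 points at 0.3 with change only. If the covariates are unrelated to outcome, the rule costs nothing and fixed adjustment would lose 1 to 2 points. Type I error stays at about 5 to 6%.

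These sizes rest on assumptions that are not in the document: the correlations, independent covariates, a 0.05 screening level, one-at-a-time testing and complete data. With the 25% attrition that the plan allows for, the cancellation in step 3 is no longer exact.

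**What to change.** Before the 5-month data are analysed by arm, and as a dated amendment, specify one primary model: group, time, group-by-time, all four named covariates, and a covariate-by-visit term for each, kept whatever their p-values. Take covariate-by-treatment terms out of the primary model and leave them to the moderator analysis. Age already sits there with its own median split and a 0.10 threshold, so at present its interaction with treatment is tested under two rules. Report the model without covariates as a sensitivity analysis, so that readers can see what adjustment did. State in the amendment that outcomes by arm had not been seen when it was made, if that is so.

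The sample size does not change. The cost is a paragraph of text, the ethics approval and registry update that the Study design section requires for any modification, and about 1 to 2 points of power if the covariates prove unrelated to outcome.
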